#### 12.2.12 Returning Investigational Product and assessing compliance

The sponsor shall withdraw and discard the Investigational Product if the clinical trial is discontinued or terminated, or if the clinical trial representative fails to perform the test according to the protocol. After consultation with the investigator, the clinical trial drug manager shall return the returned clinical trial drug to the sponsor after the use of the unused Investigational Product and the clinical trial patient, and preserve the return certificate. The returned investigational Product shall be disposed of or disposed of in accordance with the client's internal regulations.

###### Confirm medication compliance of Investigational Produc

The study patients will return the empty containers with the Investigational Product taken at Visit 2 (0weeks), the unused medicines, and the recorded medicines daily record, and the research coordinator will return the quantity of medicines prescribed at Visit 2 Determine the quantity of Investigational Product taken by the subject of the clinical trial and record the adherence compliance on the case report sheet as follows. The medicinal compliance of the Investigational Product is considered to be "compliant" if it is> 80%.

Compliance (%) = Number of Investigational Products Taken / Number of Investigational Products Taken X 100

- - 1. **Assessing Adverse Events**

Adverse events are closely monitored from the time of administration to the end of the clinical trial. In the event of an adverse event, the date and time of the adverse event, the extent and consequences of the adverse reaction, the measures taken in relation to the Investigational Product, the causal relationship with the Investigational Product, the name of the suspected drug other than the test drug, and details of the contents are recorded. After the visit, the adverse reaction should be immediately reported to the researcher, the clinical trial patient should be trained so that the patient can be admitted to the clinic, and the researcher should be contacted. The evaluation, recording and treatment of detailed adverse events is in accordance with section 16.3.

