**Protocol Outline**

| Study Title | A multi-center, randomized, double blind, placebo control, parallel design, phase 2b trial to evaluate the efficacy and safety of PGA (Poly-gamma-glutamic Acid) for the fertile women with Cervical Intraepithelial Neoplasia(CIN I) |
| --- | --- |
| Study Phase | Ⅱb |
| Study design | Randomized, Double-blind, Placebo-controlled, Parallel-group |
| Investigators/ Site Name | [name], PhD / The Catholic University of Korea Seoul St. Mary's Hospital  [name], PhD / Korea University Guro Hospital  [name], PhD/ Cheil General Hospital and Women’s Healthcare Center  [name], PhD/ Keimyung University Dongsan Medical Center  [name], PhD/ CHA Gangnam Medical Center, CHA University  [name], PhD/ Gangseo MizMedi Hospital |
| Sponsor | BioLeaders Corporation |
| Purpose | This study is to compare the regression rate of Cervical Intraepithelial Neoplasia (CIN1) between the treatment group and the control group. |
| Investigational Product | - Experimental: Poly-gamma-glutamic acid 1,500 mg  - Comparator: Placebo  - Dosage schedule: 1,500 mg in 100mL po q.d. before bedtime for 4 weeks (28 days) |
| Indication | Women aged 20-49 years with HPV positive CIN 1 |
| Inclusion Criteria | 1. Fertile female aged between 20 and 49  2. Patients who are diagnosed as Cervical intraepithelial neoplasia 1 (CIN1)  3. Patients who are infected with HPV (Human Papilloma Virus) positive (+)  4. White Blood Cell Count(WBC) over 4 10^3^/ul, Hemoglobin above over 9.0g/dL Platelet over 150 10^3^/uL and ANC (Absolute Neutrophil Count) over 1,500 10^6^/L  5. AST (Aspartate Aminotransferase) no less than 4 times higher than normal ALT (Alanine Aminotransferase) no less than 4 times higher than normal  6. Normal for EKG (Electrocardiography) and no active disease detected trough chest X-ray  7. Be informed of the nature of the study and will give written informed consent |

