| Statistical analysis | 1. General principles  Analyses will be descriptive in nature. Descriptive analyses will include the number of observations, mean, standard deviation, median, range, and interquartile range for continuous variables and the number and percent for categorical variables.  2. Populations  - ITT(Intent-to-Treatment): Defined as all assigned patients. However, patients who did not take the investigational product at least once in the ITT group should be excluded from the analysis group.  - PP(Per Protocol): PP analyses exclude all protocol major violation, including anyone who did not adhere to treatment, switched groups, or missed measurements.  - The final evaluation will be based on the results of the ITT group analysis.  3. Safety analysis  After agreeing to participate in the study, the study will be defined as the whole box of randomized, at least one investigational product.  4. Primary efficacy variable analyses  In the baseline, 3 months after the administration of CIN I, the patient was judged to be cured to normal, and the response rate between the PGA group and the control group was compared.  The evaluation of the healing rate between the groups is based on the method proposed by Jung (2008). When the results were confirmed by selecting 43 patients in each group, as in the previous step, the difference in the number of patients. In the case of less than 2 persons (PGA group-Control group), it was judged that there is no effect of PGA, and the present study is terminated. If there are more than 2 difference in level 1, 37 patients per group are recruited. In case of more than +11 patients who were judged as Histologic resolution by 80 patients per group, Histologic resolution of CIN. It is judged that there is an effect of PGA. If there is less than +11, it is concluded that the effect of PGA is not ultimately.  5. Secondary efficacy variable analyses  Secondary efficacy variable 1: Reid Colposcopic Index  0-2 Score: Likely to be CIN I  3-4 Score: Overlapping lesion - likely to be CIN I or CIN II  5-8 Score: Likely to be CIN II  The comparison between the baseline scores and the difference of the scores after 12 weeks will be confirmed through the t-test or the Wilcoxon rank sum test. In addition, considering the multinomial distribution of the grading system (0-2, 3-4, 5-8 points), the cumulative or ordinal logistic model of the changes in the grading system after 12 weeks compared to baseline.  Secondary efficacy variable 2: Pap Smear Test  The reading standard is based **on the 2001 Bethesda System for Reporting Cervical Cytologic Diagnoses**. The results of the study were divided into 6 stages: Negative, ASC-US, ASC-H, LSIL, HSIL, and Invasive cancer (Cervical carcinoma). Considering the multinomial distribution, And the cumulative or ordinal logistic model is used to analyze changes in the classification stage 3 months after the baseline.  Secondary efficacy variable 3: HPV DNA Chip Test  The HPV DNA Chip Test is a test to determine the type of virus infection. It is classified as positive or negative according to the test result. GEE (Generalized Estimating Equation) or Generalized Linear Mixed Model is considered to determine time-dependent changes, group-to-group differences, and time-to-group interactions for baseline versus measured clearance.  Secondary efficacy variable 4: HPV HC Ⅱ assay  GEE (Generalized Estimating Equation) or Generalized Linear Mixed Model is considered to determine time-dependent changes, group-to-group differences, and time-to-group interactions for baseline versus measured clearance.  Secondary efficacy variable 5: NK cell activity  To compare the results of NK cell activity measured at 4 weeks, 8 weeks, and 12 weeks versus baseline (0 week), the mean difference between the baseline and 12-week NK cell levels was calculated as t - Black or Wilcoxon rank sum test.  Secondary efficacy variable 6: MHC class II CD8, CD56 population  GEE (Generalized Estimating Equation) or Generalized Linear Mixed Model is considered to determine time-dependent changes, group-to-group differences, and time-to-group interactions for baseline versus measured clearance.  6. Safety analyses  All safety data, including all adverse events collected from patients, clinical laboratory test results, 12-lead ECG, and vital signs (blood pressure and pulse rate) are performed.  1) Adverse events  Summarize the adverse events observed following administration of the investigational product. The number of cases and the number of patients who experienced an adverse reaction, abnormal drug response, SAE, death, adverse events n that caused discontinuation of clinical trial, and / or "other significant adverse events (OAE) do. The number of patients who received each of the abnormal responses was also summarized by body-organ system (SOC), recommended language, and maximum severity for each treatment group. In addition to the summary statistics, the incidence or incidence of adverse events in the group are analyzed using Chi-squared test, Fisher's Exact test, or Poisson test.  2) Vital signs and laboratory tests  The results were analyzed by Chi-squared test, Fisher's Exact test, or Poisson test for each group of 12-lead ECG abnormalities at each time point. A summary statistic is presented and, if necessary, GLM or GLMM methods are used to perform group comparisons. |

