### 7.3 Packaging and Labeling

#### 7.3.1 Packaging of Investigational Product

It is a bottle containing liquid formulation and packed in 100mL unit which can be taken once.

To avoid distinction between the test drug and the reference drug, the drug should be packed in a brown glass bottle of the same outline in the same volume to maintain double-blindness.

The payment package at the time of dispensing the clinical trial drug will include an extra five days for four weeks.

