**14.2 Analysis exclusion criteria**

In case of a violation of a critical clinical trial plan, the patient should be excluded from the PP analysis.

1) If the patient's compliance with the Investigational Product is less than 80%

2) In case of violation of selection criteria and exclusion criteria during the test

3) In combination with drugs that may affect the efficacy evaluation

4) When the validity evaluation item inspection (visit 1) is not carried out

5) If you visit due to visiting date

Other violations of the clinical trial protocol, which are considered to have no effect on the interpretation of the study results, must be clearly stated in terms of the violation or delay and the reason and the researcher, sponsor, monitor personnel and statisticians and to include them in the PP analysis.

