###### 15.3.2 Definition of analytical group

The analytical groups needed to assess efficacy and safety in this trial were performed in both the ITT and PP assay groups as defined below for efficacy assessments in accordance with national and international standards, Define the analysis and evaluate it as a reference.

Efficacy analysis group:

- Intent-to-Treatment (ITT) group: Defined as all subjects assigned to randomization after agreement to participate in the study. But patients who did not take the study drug at least once in the ITT group will be excluded from the analysis group.

- PP (Per Protocol) group: defined as the total subjects who completed the clinical study according to the study plan without any violation of the important research plan presented in 14.2 until the end of the study after the consent to participate in the study.

- In the efficacy evaluation, all the analyzes are performed in the ITT group and the PP group, and the final evaluation is decided according to the results of the ITT group analysis. If the results of the ITT group and the PP group are different, an additional analysis will be conducted exploring why the two analyzes are different.

Safety evaluation analysis group:

After agreeing to participate in the study, they will be defined as the whole subjects who were randomized and who took the research drug at least once.

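### The compliance formula divides a count by itself, so the 80% per-protocol exclusion cannot operate, and the protocol does not settle whether the denominator is 28 or 33

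*Protocol*

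**What the plan says.** Under the compliance heading in Protocol 12.2.12, patients return empty containers, unused product and a daily record. The coordinator works out how much was taken and records compliance on the case report form by this formula: "Compliance (%) = Number of Investigational Products Taken / Number of Investigational Products Taken X 100". A patient counts as compliant above 80%. The sentence leading into the formula is garbled, but it refers to the amount supplied at the start: "the research coordinator will return the quantity of medicines prescribed at Visit 2".

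The result feeds the PP set. Section 14.2 item 1 excludes a patient whose "compliance with the Investigational Product is less than 80"%. Section 15.3.2 defines the PP group as those who completed the study "without any violation of the important research plan presented in 14.2". The Protocol Outline describes PP exclusions more loosely, "including anyone who did not adhere to treatment, switched groups, or missed measurements", with no threshold.

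Two counts compete for the denominator. The Outline gives the regimen as "1,500 mg in 100mL po q.d. before bedtime for 4 weeks (28 days"), which is 28 doses. Section 7.3.1 says the pack handed out "will include an extra five days for four weeks". On the weight of the PP set, 15.3.2 states that "the final evaluation is decided according to the results of the ITT group analysis".

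**The concern.** A ratio of a quantity to itself carries no information. Followed literally, it classes every patient who took any product as fully adherent and leaves 14.2 item 1 with nothing to exclude. The general wording in the Outline would still point to removing non-adherent patients, but someone would have to decide, patient by patient, what non-adherent means.

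The error also cannot be repaired with certainty from the text. Replacing the lower term with the amount prescribed at Visit 2 is the obvious guess, but the protocol does not say whether that amount includes the five spare bottles. The two readings give different cuts. Different sites, or an analyst working after the fact, could choose differently and arrive at different PP sets. Section 15.3.2 runs every efficacy analysis in both ITT and PP and calls for further exploration when the two disagree, so PP membership should be fixed in advance.

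**Working it through.** **Inputs**

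- Formula as printed: taken / taken × 100 (12.2.12).
- Threshold: compliant above 80% (12.2.12); excluded from PP below 80% (14.2 item 1).
- Scheduled doses: 28 (Protocol Outline, Investigational Product).
- Bottles dispensed: 28 + 5 = 33 (derived from 7.3.1).
- Visit 3, when product is returned and compliance assessed: 4 weeks ± 5 days, so day 23 to day 33 (12.3).

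**The formula as printed**

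For any count x above zero, x/x × 100 = 100%. Taking 1, 10, 22 or 28 doses gives 100% each time; zero doses gives 0/0, which is undefined. No patient can fall below 80%.

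**The cut under each denominator**

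- Denominator 28: 0.80 × 28 = 22.4, so at least 23 doses are needed (23/28 = 82.1%; 22/28 = 78.6%).
- Denominator 33: 0.80 × 33 = 26.4, so at least 27 doses are needed (27/33 = 81.8%; 26/33 = 78.8%).

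Women who took 23, 24, 25 or 26 doses are in the PP set on 28 and out of it on 33. Neither cut is a whole number of doses, so the different wording of the threshold in 12.2.12 and 14.2 makes no difference under either denominator.

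**Attending early within the Visit 3 window**

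Assume the first dose is taken on the evening of day 0, one dose is taken each evening, none is missed, and product is returned at Visit 3. Doses taken by day d are then min(d, 28).

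| Visit 3 on day | Doses | On 28 | On 33 |
|---|---|---|---|
| 23 | 23 | 82.1% | 69.7% |
| 24 | 24 | 85.7% | 72.7% |
| 25 | 25 | 89.3% | 75.8% |
| 26 | 26 | 92.9% | 78.8% |
| 27 | 27 | 96.4% | 81.8% |
| 28 or later | 28 | 100.0% | 84.8% |

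On 33, a woman who missed nothing and came on day 23 to 26, inside the permitted window, would be excluded. On 28 she stays in. A complete 28-dose course scores only 84.8% on 33. These results favour 28.

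**The case against.** The strongest reply is that this is residue from translation and not a fault in the rule. The English text is visibly translated, and other garbled lines have an obvious intended meaning. The same paragraph collects empties and unused bottles and mentions the amount prescribed, so a coordinator would hardly compute a number over itself. Nor do the documents show that sites worked from this English line. All of that is fair. It lowers the weight of the point but does not remove it: the protocol prints an operative rule that is wrong as it stands, and no correct version appears elsewhere in it.

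The reply continues that 33 is the weaker reading. The course is fixed at 28 days and the extra five are described as extra, so overage is the natural interpretation. I agree that it is. But the reference to the amount prescribed at Visit 2 gives 33 some support, and nothing in the text rules it out.

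Finally, 28 has rough edges. A woman seen on day 23 who missed one dose scores 22/28 = 78.6% and leaves the PP set, although she took 22 of the 23 doses due (95.7%). One who took all 33 bottles would score 33/28 = 117.9%. Section 12.2.15 describes dosing as running from Visit 2 to Visit 3, so days to Visit 3 is a third candidate. None of this defeats 28. Twenty-two doses is in fact less than 80% of the planned course, a score above 100% does not touch the lower cut, and a third candidate is one more reason to print a single denominator.

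**Conclusion.** The point holds, as a minor one. That the printed formula always yields 100%, and so disables 14.2 item 1, is certain. That the denominator is unsettled is also correct, though 28 is the more natural reading. The choice moves the cut by four doses, from 23 to 27.

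The consequence is confined to the supportive PP set. The ITT analysis decides, so the two-stage decision on differences of +2 and +11 responders is unaffected, and the rule applies equally to both blinded arms. How many women would change status cannot be estimated, because the protocol gives no distribution of visit dates or doses taken. The figure of 33 is derived, and the attendance table rests on the dosing assumptions stated with it.

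**What to change.** In 12.2.12, replace the formula with: Compliance (%) = number of doses taken / 28 scheduled doses × 100. Add one sentence saying that the five spare bottles are overage and are not counted in the denominator. Doses taken can be counted as bottles dispensed minus bottles returned unused. Keep the assessment at Visit 3; with 28 below the line, a woman seen on day 23 who missed no dose scores 82.1% and stays in the PP set.

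The cost is one corrected line and one added sentence. Visits, flow charts, product return and supply do not change.

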#### Concomitant medication investigation

During the clinical trial period, drugs other than Investigational Product should not be administered. Therefore, sufficient training for clinical trial subjects should be provided. It is also necessary to educate the researcher to contact the researcher if it is necessary to take medication.

If the drug administered without judgment is expected to have an impact on the efficacy and safety of the trial, the patient will be disqualified. All medications and causes of administration should be investigated through written interviews and charts of subjects and recorded in the case record. The following drugs are prohibited in this trial.

1) Steroids: Betametasone, Dexametasone, Prednisolone, Hydrocortisone, etc., except when except when applied locally to skin or eyes.

2) Immunomodulators: growth hormone, EPO (Erythropoietine), albumin preparations, transfusion of whole blood and leukocyte components, etc

3) Others: Supplements and vitamin preparations other than clinical trial drugs. Chinese medicine

#### 12.2.15 Check Cervical intraepithelial neoplasia (CIN 1) progress

Observe for 8 weeks after completion of the Investigational Product from visit 2 (0 weeks) to visit 3 (4 weeks ± 5 days). At the final visit of the Visit 5 (12 weeks ± 5 days), an effective evaluation test of the cervical dysplasia including Colposcopic Biopsy is performed. If the progression is on the Colposcopic Biopsy, the standardized treatment method and terminates the clinical trial of the patient.

### 12.3. Visit schedule overview

All visits to the patients must be scheduled on a pre-scheduled basis and strictly follow the Visit Window of each visit.

The Visit Window of each visit is within 4 weeks of visit 1, 0 is weekly visit 2, 4 weeks ± 5 days of visit 3, 8 weeks ± 5 days of visit 4, and 12 weeks ± 5 days of visit 5 The total duration of the patients is 12 week.

#### Visit 1(Within -4 weeks, Screening)

If you want to participate in the clinical trial after receiving explanation of this study, write down the written consent of the patient to be tested and perform the screening procedure and examination described below. Those with clinically significant anomalies are excluded from clinical trials.

1) Written consent of clinical trial patients

2) Demographic information

3) Examination of medical history (within 2 years of related disease, within 6 months of other diseases), taking medication survey (within 4 weeks)

4) signs of vitality, physical examination, physical measurement (weight, height)

5) Laboratory test, pregnancy test

6) Electrocardiography

7) Chest X-ray examination

8) Colposcopy (Reid's Index, Biopsy)

The test result within 4 weeks before acquisition of the consent is recognized as screening test.

(However, when using the results of other institutions, the results of biopsy should be secured so that the results can be confirmed at least.)

9) Pap smear test, HPV DNA test, Hybrid Capture II assay

10) Conformity Assessment of Clinical Test Subject (Selection / Exclusion Criteria)

###### Subject Screening/Enrollment Log

###### Record the list of clinical trial patients who signed the clinical trial patients' consent form in the selection log. If the trial box is not eligible or can’t participate in this test for any other reason, the reason should be recorded.

#### Visit 2 (0 week Baseline & Treatment )

1) Final evaluation of applicability of clinical trial patients

2) Measurement of signs of vitality

3) Confirmation of Concomitant medication change

4) Assignment number

5) Prescribing and issuing of Investigational Product

6) NK cell activity and immune phenotype test

###### Review of inclusion / exclusion criteria

The inclusion / exclusion criterion is reviewed through the vital signs and clinical test results of the patient of the clinical trial, and it is decided whether or not to be selected by the suitability evaluation of the final test patient.

#### Visit 3(4 weeks ±5 days, Observation)

1) Measurement of signs of vitality

2) Confirmation of Concomitant medication change

3) Investigational Product Return and assessment of medication compliance

4) Check adverse events

5) NK cell activity and immune phenotype test

6) Laboratory inspection

#### Visit 4(8 weeks ±5 days, Observation)

1) Measurement of signs of vitality

2) Confirmation of Concomitant medication change

3) Check adverse events

4) NK cell activity and immune phenotype test

5) Laboratory inspection

